**Methods:**

This study will be a 12-week, double-blind, parallel-group, randomized, controlled trial (RCT) in which 44 patients will be allocated to ginger and placebo groups receiving basic routine treatments plus ginger or placebo capsules, respectively. The primary outcomes are inflammatory markers (TNF-α and hs-CRP) and total antioxidant capacity.

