### Hypothesis and aim

The research hypothesis addressed is that ginger supplementation along with taking standard medications improves clinical and biochemical parameters. The primary objectives of this RCT is to assay the effect of 12-week ginger supplementation on inflammatory markers (TNF-α and hs-CRP) and TAC in patients with active UC. The secondary objective will be also to determine clinical score and miR-21 expression. For all outcomes, including the primary and secondary outcomes, measurements will be made at the beginning and the end of the intervention, and changes from baseline within groups and final values between groups will be evaluated.

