### Sample size

The sample size was calculated according to primary outcomes (if data were available), and the maximum calculated sample size was considered. The sample size was based on the changes observed in the TNF-α in the study by Mozafari Khosravi [13] as a result of ginger supplementation. Considering a type I error of 0.05, a test power of 90%, and follow-up loss of 10%, the sample size required in each group was calculated to be 22 patients. To achieve the estimated sample size, all patients will be included in the study in case they meet the inclusion criteria and are willing to participate in the study.

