### Analysis

The data will be analyzed using the Statistical Package for the Social Sciences (IBM SPSS Statistics 22. Ink). Normality of all quantitative variables (age, serum level of TNF-α, hs-CRP, TAC, and expression of mir-21) will be also evaluated by the Kolmogorov-Smirnov test. For normal distribution variables, independent sample t-test and paired sample t-test will be also used to compare parameters at the beginning and the end of the study between and within groups, respectively. The Mann-Whitney U test and Wilcoxon signed-rank test as nonparametric alternatives will be further applied to compare sample parameters between and within groups, respectively. In adjusted models for confounding variables (such as the type of medication), a general linear model (GLM) (univariate type) will be used for each certain parameter to compare mean values between groups. For each certain variable (primary and secondary outcomes), the percentage change will be also calculated (i.e., by subtracting the beginning from the final value, dividing by the beginning value, and multiplying by 100) and will be compared between groups by independent sample t-test or Mann-Whitney U, as well as by GLM univariate tests. The results will be presented as the mean ± SD, and differences will be considered statistically significant at *p* < 0.05. Intention-to-treat analysis will be employed if possible.

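### Three unranked primary outcomes, each compared between groups in up to four ways at p < 0.05 with no deciding result named, take the type I error above the stated 0.05

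*Protocol article*

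**What the plan says.** **Outcomes.** The abstract states: "The primary outcomes are inflammatory markers (TNF-α and hs-CRP) and total antioxidant capacity". Under Hypothesis and aim, the primary objectives are again the effect of "12-week ginger supplementation on inflammatory markers (TNF-α and hs-CRP) and TAC in patients with active UC". Neither place ranks the three or says how many must succeed.

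**Between-group comparisons.** Hypothesis and aim gives final values as the between-group comparison and change from baseline as the within-group comparison, for all outcomes. The Analysis section then sets out, for each outcome:

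1. a t-test or, for non-normal data, a Mann-Whitney test on the values;
2. a GLM on the values, adjusted for confounders, with type of medication as the only example;
3. and 4. percentage change, which "will be compared between groups by independent sample t-test or Mann-Whitney U, as well as by GLM univariate tests".

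Within-group paired tests are added to these.

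**Threshold.** One rule covers everything: "differences will be considered statistically significant at" p < 0.05.

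**Sample size.** The section says a size was calculated for the primary outcomes that had data and the largest was taken. It then says: "The sample size was based on the changes observed in the TNF-α". With a type I error of 0.05, 90% power and 10% loss, "the sample size required in each group was calculated to be 22 patients".

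**The concern.** The trial is sized at a type I error of 0.05, but the analysis text offers several routes to a significant primary result and does not choose among them. With three outcomes, each open to comparison as values or percentage change and with or without adjustment, there are 3 × 4 = 12 between-group p-values on primary outcomes. Any of them could be reported as the finding without departing from the written plan. A reader of the results would assume a 5% chance of a false claim, and the rule as written does not deliver that. Taking the largest sample size across outcomes protects power. It does nothing for the type I error.

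**Working it through.** **The plan's own figure.** The effect size and SD behind 22 per group are not given, so the figure cannot be reproduced, only back-solved. With two-sided 0.05 (sidedness is not stated), 90% power and the normal approximation, d = (1.960 + 1.282) × √(2/n):

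- n = 19 evaluable: 19/0.90 = 21.1, rounded up to 22; d = 1.05.
- n = 20 evaluable: 20 × 1.10 = 22; d = 1.03.

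The type I error argument does not depend on this. The cost of the Holm option does.

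**Counting the tests.** The t-test and Mann-Whitney test are alternatives, so they count as one. What multiplies is values versus percentage change and unadjusted versus GLM: 2 × 2 = 4 per outcome, 12 for three outcomes.

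**One test per outcome, independent outcomes.** 1 − 0.95³ = 1 − 0.857 = 14.3%.

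**Correlated outcomes and repeated tests.** The four tests on one outcome share data, so the independence formula for 12 tests (1 − 0.95¹² = 46%) is too high. Simulation under no effect is needed. A false claim is counted if any of the tests considered gives p < 0.05.

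*Normal data, 22 per group, pre-post correlation 0.3 to 0.8, 2,000 trials per scenario:*

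| Correlation between markers | One test per outcome | Any of 12 |
|---|---|---|
| 0 | 13.5-13.9% | 24-27% |
| 0.3 | 12.6-13.0% | 24-25% |
| 0.6 | 10.5-10.9% | 21-22% |
| 0.9 | 7.0-7.4% | 15-16% |

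*Independent outcomes, 22 per group, binary medication covariate in the GLM, pre-post correlation 0.3 to 0.7, 40,000 replicates:*

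| Data | Four tests, one outcome | Any of 12 |
|---|---|---|
| Normal | 9.7-10.5% | 26-28% |
| Lognormal (log-SD 0.6 or 1.0) | 11.6-12.5% | 31-33% |

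The second column follows from the first. For example, 1 − (1 − 0.125)³ = 33%.

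If GLMs with baseline as a covariate are run in addition, the any-test rate for independent outcomes rises to 30-32% (normal) and 34-38% (lognormal).

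A smaller run (20 per group, 500 trials per scenario, pre-post correlation 0.55, normal or lognormal with log-SD 0.5, marker correlation 0 to 0.6) agrees: 10-16% for one test per outcome, 9-12% for four tests on one outcome, and 25-31% for all 12.

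**After correction.** One named outcome with one named test gives 5%. Three outcomes at 0.05/3 = 0.0167, one test each, give 1 − (1 − 0.0167)³ = 4.9% if independent, and at most 5% in any case. At 0.0167 with the back-solved d and 19-20 evaluable per group, power per outcome is about 80%. Restoring 90% would need about 25-26 evaluable per group: 25/0.90 = 27.8 and 26/0.90 = 28.9, so 28-29 with 10% loss.

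**The case against.** **The aims already choose final values.** This is the strongest point. It is tempting to say that no between-group comparison is named and that all 12 p-values stand as equal primary claims. The documents do not support that: Hypothesis and aim gives final values, and the Analysis section brings in percentage change as something done in addition. But the aims do not make final values the sole deciding analysis, and they leave open unadjusted versus GLM. Restricting to final values with both tests still gave 14-16% across the three outcomes (20 per group, log-SD 0.5, pre-post correlation 0.55, binary medication covariate).

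**The size is assumption-driven.** A reader might take 14% as a floor or 33% as the trial's actual error rate. Neither follows. Correlated markers with one test each fall below 14%. The value of 33% belongs to skewed, independent outcomes, and a freer covariate choice can exceed it. What stands is that every scenario computed is above 5%.

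**Success on all three might be intended.** The document does not say so. That rule would remove the inflation, but 90% power per outcome would become 0.9³ = 73% jointly if the outcomes were independent, so the stated power would not describe it.

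**The sample size shows TNF-α to be the one confirmatory test.** It might be inferred that the size rests on a single 5% test of TNF-α. The section names no test, and TNF-α emerged only after comparing the primary outcomes that had data. It is the basis of the size, not a declared sole primary endpoint.

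**The analysis plan is not shown.** Multiplicity rules and the primary model are often set there, and their absence from an article would be no finding. Here the article itself fixes three unranked primaries, the added comparisons and one threshold for all of them. A later hierarchy would have to change that text.

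**Conclusion.** The point holds. Three unranked primary outcomes, up to four between-group comparisons of each and a uniform p < 0.05 give a type I error above the stated 0.05, provided that a positive result on any one outcome counts as success. The documents state no other rule. The size is 14.3% for one test on each of three independent outcomes, about 7-13% at marker correlations of 0.9 to 0.3, and roughly 15-33% if any of the 12 comparisons may be used. Only the 14.3% is exact, and it too requires independence. The other figures rest on assumed correlations, distributions and covariates and should be read as illustrations. The direction does not depend on those choices in any scenario examined.

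**What to change.** Before unblinding, amend the Analysis section and the registry entry:

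- Name TNF-α as the single primary outcome, since the sample size was based on it.
- Name one primary test: final value, ANCOVA adjusted for baseline, two-sided 0.05, with any further covariates listed in advance.
- Test hs-CRP and then TAC in fixed sequence, each at 0.05 and only if the preceding test is significant.
- Label the other comparisons as supportive, including unadjusted tests, percentage change and within-group tests.

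This needs no extra patients. The article describes the trial as ongoing and keeps the codes confidential until all patients have completed, so on its own account the change is feasible. The price is that hs-CRP and TAC can no longer carry a stand-alone claim at 5%.

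The alternative is to keep all three primary with Holm's procedure, one named test each. The error is then controlled, but power per outcome at the strictest step (0.0167) is about 80% and not 90%, under the back-solved d of about 1.03-1.05, which is an assumption. The stated power should then be restated, or the size raised to about 28-29 per group.

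### Mean ± SD is fixed for all results although non-normal markers go to rank tests, and no baseline-adjusted between-group estimate is named

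*Protocol article*

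**What the plan says.** All of the following is in the protocol article.

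- **Normality check (Analysis).** "Normality of all quantitative variables (age, serum level of TNF-α, hs-CRP, TAC, and expression of mir-21") is to be examined by the Kolmogorov-Smirnov test. The list includes all three primary outcomes (TNF-α, hs-CRP and TAC).
- **Rank route (Analysis).** Normal variables go to t-tests. For the others, "The Mann-Whitney U test and Wilcoxon signed-rank test as nonparametric alternatives will be further applied to compare sample parameters between and within groups, respectively".
- **Adjusted model (Analysis).** A univariate GLM "will be used for each certain parameter to compare mean values between groups". Type of medication is the only adjustment variable given, and it is given as an example.
- **Percentage change (Analysis).** This is calculated for every primary and secondary outcome and "will be compared between groups by independent sample t-test or Mann-Whitney U, as well as by GLM univariate tests".
- **Presentation and decision rule (Analysis).** "The results will be presented as the mean ± SD", and "differences will be considered statistically significant at" p < 0.05. No exception is made for variables tested by ranks.
- **Comparisons intended (Hypothesis and aim).** All outcomes are measured at the start and end of the intervention, and "changes from baseline within groups and final values between groups will be evaluated".

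**The concern.** The presentation rule and the test rule in the Analysis section do not fit each other. A variable reaches the rank tests because the plan has judged it non-normal, yet it must still be printed as mean ± SD. A Mann-Whitney p-value concerns the ordering of values in the two arms, whereas mean ± SD describes location and spread in a way that suits roughly symmetric data. A reader could then see two means whose gap does not correspond to the p-value beside them. The rule reaches the primary outcomes, because all three are on the normality-check list.

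A related weakness lies in the between-group comparison. The trial asks how much ginger changes the markers relative to placebo. The most direct answer is a week-12 difference adjusted for the patient's own starting value, with its uncertainty. The plan names unadjusted tests of final values, tests of percentage change, and a GLM for confounders. Baseline values will be collected, but the text does not name them as a covariate.

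**Working it through.** The plan gives no figure for this point, and no distribution for any marker, so there is nothing of its own to reproduce. The sizes below rest on stated assumptions.

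**1. Mean ± SD for a skewed marker.** Assume a log-normal marker with median 1 and log-scale SD s. Then mean = exp(s²/2), SD = mean × √(exp(s²) − 1), and IQR = exp(±0.6745 s).

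| s (assumed) | Mean ± SD | Mean − SD | IQR | Share below the mean |
|---|---|---|---|---|
| 0.3 | 1.05 ± 0.32 | 0.73 | 0.82–1.22 | 56% |
| 0.5 | 1.13 ± 0.60 | 0.53 | 0.71–1.40 | 60% |
| 0.8 | 1.38 ± 1.30 | 0.07 | 0.58–1.72 | 66% |
| 1.0 | 1.65 ± 2.16 | −0.51 | 0.51–1.96 | 69% |
| 1.2 | 2.05 ± 3.69 | −1.63 | 0.45–2.25 | 73% |

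At the low end the usual summary does little harm. From about s = 1.0, mean minus SD is negative, which is impossible for a concentration, and more than two thirds of patients lie below the printed mean.

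**2. Percentage change under the same rule.** Assume no true change and a within-patient correlation of 0.5 on the log scale. The log ratio of final to baseline value then has variance 2s²(1 − 0.5) = s², so the median change is 0% and the mean change is exp(s²/2) − 1:

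- s = 0.5: exp(0.125) − 1 = 13%
- s = 0.8: exp(0.32) − 1 = 38%
- s = 1.0: exp(0.5) − 1 = 65%

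Both arms would be displaced alike, so this alone does not create a group difference. It would, however, print an apparent rise where the typical patient has not changed.

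**3. Precision available for a between-group estimate.** Sample size gives 22 per group and 10% loss: 22 × 0.9 = 19.8, so about 20 per arm. The 95% half-width for an unadjusted difference in means is t(0.975; 38) × √(2/20) = 0.640 SD. With 22 per arm it is 0.608 SD, and with 19 it is 0.658 SD.

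**4. What baseline adjustment can add.** In a linear model for the week-12 value, entering baseline multiplies the standard error by about √(1 − r²), where r is the baseline–final correlation. At r = 0 there is essentially no gain. At the assumed r = 0.5 the factor is √0.75 = 0.866, and the half-width falls from 0.640 to about 0.640 × 0.866 = 0.55 SD. The gain grows with r. The article gives no value for r.

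**The case against.** The strongest objection is that the article does not say intervals or differences will be left out. It states a format for results without the word *only*, and it plans a GLM that compares means between groups and can yield a difference with a CI. A journal article commonly leaves such detail to a full protocol or SAP. This stands. A reader might infer that the trial will report no between-group effect with a confidence interval, but that would be a conclusion drawn from silence.

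Three further objections also hold.

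- **Skewness is not shown.** A reader might infer that the markers will be misdescribed. That follows only for a marker that proves clearly skewed. One that passes the normality check is suitably shown as mean ± SD alongside its t-test.
- **The unadjusted difference is recoverable.** With mean, SD and n per arm, a reader can compute the difference and its standard error, √(SD₁²/n₁ + SD₂²/n₂). So mean ± SD does not hide the unadjusted effect. It does not yield the baseline-adjusted one.
- **The ±0.64 SD half-width does not measure the fault.** It reflects the number of patients and is the same under any reporting format.

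What the objections do not remove is the mismatch within the Analysis section. The mean ± SD rule is stated, has no exception, and does not suit the variables that the same paragraph sends to rank tests.

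**Conclusion.** The point holds in a limited form and is minor. The stated presentation rule misfits the plan's own rank-test route for any marker that fails the normality check. Under the log-normal assumption, the effect runs from negligible (1.05 ± 0.32 at log-SD 0.3) to misleading (1.65 ± 2.16 at log-SD 1.0). Where TNF-α, hs-CRP, TAC and miR-21 fall in that range cannot be told from the article.

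Separately, the named between-group comparisons can be improved with data the trial already collects. No baseline-adjusted estimate is named, although the article does not rule one out. The consequences concern reporting and, through baseline adjustment, precision. They do not affect the validity of the tests or the planned 22 per group.

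**What to change.** Amend the Analysis section as follows.

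1. For TNF-α, hs-CRP and TAC, and likewise for the secondary outcomes, fit the planned GLM to the week-12 value with the baseline value as a covariate. Report the adjusted ginger-minus-placebo difference with its 95% CI.
2. For markers that prove skewed, fit that model on the log scale and report the ratio of geometric means with its 95% CI.
3. Describe those markers by median (IQR) or geometric mean, and keep mean ± SD for variables that are roughly symmetric.

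This takes a few sentences and no new measurements, since baseline and final values are already planned for every outcome. The cost is a little more analysis work, and a ratio scale for skewed markers that some readers will find less familiar than a difference. Sample size and type I error do not change.

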### Safety, adverse effects, and data monitoring

No side effects have been reported for 3 g/d consumption of ginger capsules [20]. However, any possible complications will be reported to the Medical Ethics Committee of Ahvaz Jundishapur University of Medical Sciences.

## Discussion

Use of alternative or complementary therapies (CAMs) has emerged as a common approach in gastrointestinal diseases. Therefore, different types of CAMs exist, and among them, herbal remedies seem much more appropriate for intestinal inflammation because of their primarily supposed safety and efficacy. Given their different active components, herbal remedies may simultaneously target multiple inflammatory response paths and mediators. However, most herbal remedies have an experimental basis, and proper experimentation on their safety and efficacy is needed to determine whether they can be considered as an appropriate strategy or not for improvement of IBD patients. Complications of medications also require an investigation into possible promising complementary agents. In this respect, ginger presents promising results in experimental models of UC. Therefore, this RCT will be designed to investigate the effect of ginger in patients with UC.

## Trial status

This trial is in the ongoing phase. The protocol version number is NCR-9722, and it was approved in March 2019. Patient recruitment began in July 2019 and is expected to be completed by May 2020.

## Data Availability

The datasets generated and analyzed during the current study are not publicly available because this is a protocol, and the results are secure before publishing; however, these data are available from the corresponding author on reasonable request.

## Abbreviations

IBDs: Inflammatory bowel diseases
IPAQ: International Physical Activity Questionnaire
PMS: Partial Mayo score
UC: Ulcerative colitis
